### **5.1 Lab procedures**

**Enumeration of Bacteria Burden:** The swab in 3ml PBS will be vortexed and using the stock suspension, serial dilutions from  $10^{-2}$  to  $10^{-8}$ . Hundred microlitres of serial dilutions will be transferred into sterile Petri dishes and inoculated by the pour plate method using Plate Count Agar for total aerobic counts (oxid) after incubation at 37°C for 18-24 hours. After incubation, the plates will be examined using a colony counting chamber (Gallenkamp, UK) and those with colony counts between 30 and 300 will be selected for computing CFU/ml by multiplying the counts by the dilution factors. The lesion from which the sample was taken will then be classified as clean, contaminated or infected.

**Isolation of Specific Aerobic Pathogens:** The stock solution will then be centrifuged at 8,000g for 30 minutes and the sediment will be cultured under aerobic conditions on blood, chocolate and MacConkey agar for bacteria isolation. Isolates will be identified by specific biochemical analysis following gram staining and confirmed by MALDI-TOF mass spectrometry.

**Anaerobic Bacteriology:** The sample in the cooked meat medium will be incubated at 37°C for 48-73 hours. The media will then be examined for signs of growth such as turbidity, proteolysis and saccharolysis. Tubes with signs of growth will then be subcultured onto blood agar with a metronidazole disc placed on it to check for resistance. This is placed in a glass jar with an anaerobic

gas pack and incubated at 37°C for 48-72 hours; bacteria growth will be examined for colonial morphology and susceptibility to metronidazole and gram reaction. Final identification will be done by MALDI-TOF mass spectrometry.

**Blood Culture:** The culture bottles will be incubated aerobically at 35- 37°C for up to 7 days and daily checked for signs of growth such as turbidity of the broth, growth on the agar slope or a pellicle on the surface of the broth. Subculture will be done onto Blood agar (35-37°C for 18-24 hours aerobically), Chocolate agar (35-37°C for 48 hours anaerobically) and MacConkey agar (37°C for 18-24 hours aerobically). Growth will be identified using gram staining and standard biochemical analysis depending on the gram reaction.

**Mycolactone analysis:** Extracted lipids will be analyzed by liquid chromatography-mass spectrometry (LC-MS).

**Histopathology:** Tissue samples will be fixed in 4% neutral-buffered paraformaldehyde for 24h and subsequently transferred to 70% ethanol for transport. Samples will be dehydrated, embedded in paraffin, cut into 5 mm thin sections and retrieved on glass slides. After dewaxing and rehydration, sections will be stained with haematoxylin/eosin (HE) and Ziehl-Neelsen (ZN) staining of AFBs. Immunohistochemistry will be performed with antibodies specific for markers of inflammation and wound healing

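### The CFU/ml formula omits the 0.1 ml plated volume, so as written absolute bacterial loads come out tenfold (1 log10) too low

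*Protocol*

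**What the plan says.** The rule is in the Protocol, section 5.1 (Lab procedures), in the paragraph on enumerating bacterial burden. The steps come in this order:

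- Suspension and dilution: "The swab in 3ml PBS will be vortexed and using the stock suspension, serial dilutions from" 10^-2 to 10^-8.
- Plating: "Hundred microlitres of serial dilutions will be transferred into sterile Petri dishes and inoculated by the pour plate method".
- Calculation: "those with colony counts between 30 and 300 will be selected for computing CFU/ml by multiplying the counts by the dilution factors".
- Use of the result: "The lesion from which the sample was taken will then be classified as clean, contaminated or infected".

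The plated volume does not enter the calculation here or elsewhere in the Protocol. No cut-off is given for the three classes, and nothing says whether a cut-off would apply per ml, per swab or per wound area. The paragraph also does not say what is recorded when no plate falls within the countable range.

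**The concern.** A plate count estimates the organisms in the volume put on the plate. Here that volume is 0.1 ml, so multiplying by the dilution factor gives organisms per 0.1 ml of the undiluted suspension. The Protocol labels this number CFU/ml, and the label and the quantity differ by a factor of ten.

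Two things are at stake. Any absolute load that the study reports would be wrong by one log10 and not comparable with loads computed correctly elsewhere. In addition, the computed load is the only quantity given before lesions are sorted into three classes. If the cut-offs are in true CFU/ml and the loads are not, some lesions would fall into a lower class than they should. Secondary infection or colonisation appears in section 6 as Descriptive item 6 and Analytical items 2 and 4, and it bears on Analytical items 5 and 8.

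**Working it through.** **Inputs, all from Protocol section 5.1**

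- Suspension volume: 3 ml
- Dilutions of the stock: 10^-d, with d = 2 to 8
- Volume plated: V = 100 microlitres = 0.1 ml
- Countable range: C = 30 to 300 colonies per plate
- Class cut-offs: none given

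The Protocol contains no worked CFU/ml value, so there is no figure to reproduce. Only the formula can be checked.

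**Formulas**

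- As written: load = C x 10^d
- With plated volume: load = C x 10^d / V
- Ratio of the second to the first: 1 / V = 1 / 0.1 = 10, for every C and d

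**Results**

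| Plate | As written | Divided by 0.1 ml |
|---|---|---|
| 150 colonies at 10^-4 | 150 x 10^4 = 1.5x10^6 | 1.5x10^7 |
| 30 colonies at 10^-2 (lowest countable) | 30 x 10^2 = 3x10^3 | 3x10^4 |
| 300 colonies at 10^-8 (highest countable) | 300 x 10^8 = 3x10^10 | 3x10^11 |

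**Effect on comparisons.** On the log10 scale the error is a constant -1. For two groups or visits A and B, (log A - 1) - (log B - 1) = log A - log B. Ratios, ranks and log differences are therefore unchanged.

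**Effect on the classes.** For a cut-off T in true CFU/ml, a lesion changes class only if its true load lies between T and 10T, and the change is always downwards. The share depends on where T lies, which the Protocol does not say. As an illustration only, assume log10 load is normal with SD s and T lies k log10 units above the mean. The share moved across that one cut-off is Phi((k+1)/s) - Phi(k/s).

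- s = 1, k = 0: 0.841 - 0.500 = 0.341
- s = 1, k = 2: 0.9987 - 0.9772 = 0.021
- s = 2, k = 0: 0.191
- Over k = -2, -1, 0, 1, 2 and s = 1, 1.5, 2, the share runs from 2.1% to 34.1%. Between those grid points it can be somewhat higher: s = 1, k = -0.5 gives 0.691 - 0.309 = 0.383.
- If T was itself set on the uncorrected scale, the share is 0%.

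**Lower limit.** The least diluted plate is 10^-2 and at least 30 colonies are required. With the volume included, the lowest quantifiable load is 30 x 10^2 / 0.1 = 3x10^4 CFU/ml.

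**The case against.** **The dilution factor may already include the inoculum.** The Protocol does not define the term. If the 0.1 ml inoculum is counted as one more tenfold step, the ratio is 1.0 and nothing is wrong. This reading is possible but strained: the dilutions are named as 10^-2 to 10^-8 before any plating, and the 100 microlitres are drawn from those finished dilutions. Even if it was intended, the text would let two laboratory workers report values tenfold apart from the same plate.

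**A reader might infer that lesions are misclassified.** The Protocol does not support this. It gives no cut-off and no unit, a cut-off set on the same scale would move no lesion, and a cut-off in true CFU/ml would move only lesions within one log above it. Section 6 also never names the three-level class as the outcome of its infection and colonisation items. Smears, aerobic and anaerobic culture and histopathology supply other evidence on infection. This part of the objection stands.

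**A reader might infer that low-count swabs are dropped and clean wounds lost.** The text does not say so. It says which plates are used for the calculation and is silent on the rest, and such a swab could still be classed as clean. Handling of values below a limit may also be left to an analysis plan that is not shown. That part stands too. Adding plates at lower dilutions would be a laboratory preference, not a correction.

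**The consequences are limited.** The study is observational. The Protocol attaches no sample size calculation or designated primary endpoint to this count, and the error can be reversed from the raw counts. That lowers the priority but does not make the formula right.

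**Conclusion.** The stated rule is wrong on its plain reading. It yields CFU per 0.1 ml under the label CFU/ml, so absolute loads are exactly tenfold (1 log10) too low. This rests on one assumption: that the dilution factors are those of the named series, 10^2 to 10^8.

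Comparisons of log load between new and old cases or over time are not affected. Reported absolute loads are. Class assignment can be too low for lesions within one log above a cut-off set in true CFU/ml, but the Protocol gives no basis for saying how many, or that any are; the percentages in the working are illustrations under assumed distributions. The point is a plain correction of moderate importance, not a threat to the study's design.

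**What to change.** In section 5.1, replace the calculation with: CFU/ml of suspension = colonies x dilution factor / 0.1 ml. Recalculate any counts already recorded with the written rule, and apply the cut-offs for the three lesion classes on that same scale, stated with their unit.

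With this formula the lowest quantifiable load is 3x10^4 CFU/ml. Record a swab with fewer than 30 colonies at 10^-2 as below that limit, not as missing.

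The cost is a line or two in the Protocol or laboratory procedure and, where counts exist, multiplication by ten. No additional plates, samples or visits are needed, and no data are lost provided the counts and dilutions were kept.

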## **6 STATISTICS AND DATA ANALYSIS**

### **Descriptive**

Simple descriptive statistics will be performed with baseline variables (age, sex) and wound healing related variables (clinical response, adverse events, histopathological, microbiological and immunological parameters and features).

1. Age and sex distribution of BU patients hospitalized/attending outpatient clinic in Amasaman and Obom
2. Residence of the BU patients attending the BU Centre Amasaman/ Obom
3. Nutritional status of BU patients
4. Frequency and types of skin diseases coexisting with BU
5. Frequency of BU lesions among relatives/ family members
6. Secondary bacterial infection/ colonization at hospital entry

### **Analytical**

1. Association of histopathological and immunological parameters of wound healing with clinical signs for wound healing
2. Secondary bacterial infection / colonization over time in hospitalized patients
3. Time dependent evaluation of wound size
4. Secondary bacterial infection / colonization of wounds of NC compared to OC
5. Association between body temperature and microbiological colonisation of BU wounds
6. Evaluation of pain during wound healing
7. Definition of clinical wound healing signs in BU wounds over time
8. Determination of patient-related factors predisposing to wound infections and delayed wound healing.

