## **4 ASSESSMENT AND FOLLOW-UP**

### **4.1 Clinical and Laboratory Assessments (at enrolment)**

A) Buruli Ulcer Ward at Amasaman Municipal Hospital

- Baseline clinical examination including photographic documentation
  - Overall clinical assessment (past and present medical history, present complaints, physical examination)
  - Description of the lesion (margin of ulcer, size of ulcer / nodule [max / min diameter, size in mm^2 determined in digital images taken in a standardized format], wound exudates, epithelialisation, scarring, temperature at lesion and contra lateral)
- Laboratory tests
  - Fine needle aspiration (nodules) for Buruli Ulcer diagnosis
  - Swab samples (ulcers) for diagnosis, validation of new diagnostic procedures and for the analysis of secondary infections and for further necessary analysis
  - Punch biopsies (ulcers) for assessment of histopathological features, nature and localization of secondary infections and for markers of inflammation and wound healing
  - Blood samples for WBC, differential, HIV- test, sickle test
  - Blood samples of patients if clinically indicated for blood cultures, malaria RDT, CRP

- Blood samples from HIV positive patients for CD4 count and viral load

B) Health Centre in Obom:

Same as above

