## 4.2 Clinical and Laboratory Assessments during Follow up

Follow-ups are performed at the intervals as lined out in table 1:

A) Buruli Ulcer Ward at Amasaman Municipal Hospital

- Clinical examination and assessment
  - Clinical assessment (body temperature, weight)
- Assessment of wound healing and secondary effects
  - Description of the lesion ( size of ulcer / nodule [max / min diameter, size in mm^2 determined in digital images taken in a standardized format], epithelialisation, scarring, moisture balance, wound ground, granulation tissue, wound exudates, margin of ulcer, temperature at lesion and contra lateral, wound surface, odour, pus)
  - Photo documentation made of all lesions.
- Laboratory tests
  - Punch biopsies (ulcers) for assessment of histopathological features, nature and localization of secondary infections and for markers of inflammation and wound healing treatment success
  - Swab samples (ulcers) for analysis of secondary infections
  - Blood samples of patients with a temperature >38,5°C or clinically indicated for blood cultures, malaria RDT, WBC, differential blood count, CRP and others
  - Blood samples from HIV positive patients for repeated CD4 count and viral load
  - Tissue samples (of wound debridement, wound excision) for assessment of histopathological features

B) Health Centre in Obom: As above

All data will be directly entered into the CRF (source data)

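### Pain during healing is to be analysed but no pain measure is scheduled, and six of the twelve follow-up lesion signs are not itemised for Day 0

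*Protocol*

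**What the plan says.** Three planned analyses in Section 6 (Analytical) depend on repeated clinical observation of the wound and the patient: item 6, "Evaluation of pain during wound healing"; item 7, "Definition of clinical wound healing signs in BU wounds over time"; and item 1, "Association of histopathological and immunological parameters of wound healing with clinical signs for wound healing". Objectives 3 and 4 (Section 1.4) ask for lesions and healing parameters to be described both at entry and through follow-up, until closure or six months.

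The measurements are set out in three places.

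- **Section 4.1 (enrolment)** begins "Description of the lesion (margin of ulcer, size of ulcer / nodule [max / min diameter" and, after the size detail, ends with "wound exudates, epithelialisation, scarring, temperature at lesion and contra lateral". It also has a general history, including current complaints, and a physical examination.
- **Section 4.2 (follow-up)** has lesion size and then "epithelialisation, scarring, moisture balance, wound ground, granulation tissue, wound exudates, margin of ulcer, temperature at lesion and contra lateral, wound surface, odour, pus". The general part is limited to "Clinical assessment (body temperature, weight".
- **Table 1** has one row for wound assessment, weight and temperature. It is marked at Day 0, then weekly in Months 1 and 2 and every two weeks in Months 3 to 6. Punch biopsy is marked at Day 0 and Month 2, with further biopsies if indicated and during surgery.

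Sections 4.1 and 4.2 apply the same lists to both sites. Section 6 (Descriptive, item 3) also plans "Nutritional status of BU patients".

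**The concern.** An analysis of pain during healing needs pain recorded in a comparable way at successive visits. If a site collects only what the protocol lists, it will hold at most a free-text complaint at entry and nothing afterwards. Pain that is not asked about at a visit cannot be recovered later, so this gap cannot be left to a statistical analysis plan.

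The two lesion lists raise a related problem. Items 1 and 7 relate tissue findings and the course of healing to clinical signs, and the first biopsy is taken on Day 0. If a site works from Section 4.1 on that day, half the signs used later may have no entry value to set beside the biopsy. Secondary infection at hospital entry is also a planned description (Descriptive, item 6), yet pus and odour are among the signs not named for enrolment.

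**Working it through.** The protocol gives no figure to reproduce here. The check sets the planned analyses against the listed measurements.

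**1. Pain.** The word occurs once in the protocol shown, in Analytical item 6.

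| Place | Pain measure named | Nearest entry |
|---|---|---|
| Table 1 | none | none |
| Section 4.1 | none | current complaints in the history, unscored |
| Section 4.2 | none | none; the general part is body temperature and weight |

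Scheduled occasions, taking a month as four weeks:

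- Months 1 and 2, weekly: 2 × 4 = 8
- Months 3 to 6, every two weeks: 4 × 2 = 8
- Follow-up total: 8 + 8 = 16; with Day 0: 16 + 1 = 17

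This is a maximum, because the objectives end description at wound closure. A pain measure is named at none of these occasions.

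**2. Lesion signs.** The two lists compared as sets:

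| Sign | 4.1 (Day 0) | 4.2 (follow-up) |
|---|---|---|
| Size | yes | yes |
| Margin | yes | yes |
| Exudates | yes | yes |
| Epithelialisation | yes | yes |
| Scarring | yes | yes |
| Lesion and contralateral temperature | yes | yes |
| Pus | no | yes |
| Odour | no | yes |
| Granulation tissue | no | yes |
| Moisture balance | no | yes |
| Wound surface | no | yes |
| Wound ground | no | yes |

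Section 4.1 has 6 signs and Section 4.2 has 12. No sign is in 4.1 alone, and 12 − 6 = 6 are in 4.2 alone, so 6/12 = half of the follow-up signs are not itemised at enrolment.

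**3. Link to biopsies.** Two biopsy times are fixed, Day 0 and Month 2. One of the two therefore falls on the day governed by the shorter list. Unscheduled biopsies and surgical tissue come on top of these.

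**4. Nutritional status.** Weight is scheduled at Day 0 and at every wound assessment, and age is a baseline variable, so a crude weight-for-age description is possible. BMI is weight divided by height squared, and weight-for-height also needs height. Height is not listed in Table 1, 4.1 or 4.2, so neither index can be derived from the listed data.

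**The case against.** The best defence is that an item not listed is not necessarily an item not collected. Residence, coexisting skin diseases and lesions among relatives are also planned descriptions in Section 6, and none is itemised in Table 1, 4.1 or 4.2. The lists are evidently not exhaustive, and the CRF, into which all data go directly, is not shown. This stands to the extent that a reader should not conclude that pain will go unrecorded or that item 6 is impossible. It does not remove the gap: nothing in the protocol obliges either site to score pain at any visit.

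A reader might also infer that the six signs are recorded only after baseline. The document does not support that. Table 1 puts the Day 0 wound assessment in the same row as those at follow-up, Section 3.4 adds a guideline-based evaluation of the ulcers before enrolment, and Day 0 photographs may show some of the signs. Exudates, which are on the Day 0 list, plausibly overlap with moisture balance and pus. Neither item 1 nor item 7 specifies a change-from-baseline analysis. What remains is that neither Table 1 nor Section 3.4 itemises signs, and the one section that does so for enrolment is shorter than its follow-up counterpart.

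Finally, it would go too far to say that nutritional status has no supporting measurement. Weight is taken throughout, and the planned item is a single descriptive line with no stated index.

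**Conclusion.** The point holds in a limited form.

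- **Pain** is the firm part. A planned analysis over time has no scheduled measure at any of up to 17 occasions, so following the protocol as written does not produce a pain series.
- **Lesion signs:** the count of six out of twelve is exact for the two lists. It shows that Sections 4.1, 4.2 and Table 1 are not aligned, not that the signs will be missing on Day 0. It matters because objectives 3 and 4 start at entry and one of the two fixed biopsy times is Day 0.
- **Nutritional status** is minor: a crude description is feasible, a height-based one is not.

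These conclusions assume that sites collect what the protocol lists. CRF fields beyond those lists would reduce the practical loss, but the protocol would still need to require them. The change is worth making, since an assessment missed at a visit cannot be made up afterwards. The study is observational, and the point bears on particular secondary questions rather than on its overall validity.

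**What to change.** 1. Add an age-appropriate pain score to Table 1 and to Sections 4.1 and 4.2, at Day 0 and at each scheduled wound assessment.
2. Replace the lesion list in Section 4.1 with the twelve-sign list of Section 4.2, and state that the wound-assessment row in Table 1 means this list at every occasion, including Day 0.
3. Optionally, add height at Day 0 and name the index by which nutritional status will be described.

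The cost is a few CRF fields and a little time at visits that already take place. None of the changes requires an extra visit or an invasive procedure.

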## **7 ETHICS AND REGULATORY ISSUES**

### **7.1 Ethics Approval**

This study will be conducted in accordance with the ethical principles that have their origin in the Declaration of Helsinki and in compliance with ICH-GCP, ISO 14155-1 and -2, and the applicable laws and regulations of the participating country.

Approval of this protocol will be sought for from the:

Ethical Review Board of the Noguchi Memorial Institute for Medical Research, Legon, Ghana and of the Ghana Health Service

### **7.2 Consent**

Patients willing to participate in the study will be fully informed about the study procedures, the risks of participation and possible benefits. The explanation of the written English informed consent will be translated into the patient's spoken language when needed. In general, written informed consent will be obtained by the signature of the patient or the signature of the guardian/legal representative (in case a patient is minor) on the informed consent form or, if the patient or guardian/ legal representative is illiterate, certify their consent with a fingerprint accompanied by the signature of an impartial witness.

The right of the patient or guardian/legal representative to refuse participation without giving reasons will be respected.

All participants are free to withdraw their consent to participate in the study at any time without giving reasons and without any consequences.

The Ethics Committee(s) must approve the informed consent document to be used by the Investigator.

### **7.3 Confidentiality**

The Principal Investigator will preserve the confidentiality of participants taking part in the study.

